## Abstract

**Background:**

The burden of poverty-related infectious diseases remains high in low- and middle-income countries, while noncommunicable diseases (NCDs) are rapidly gaining importance. To address this dual disease burden, the *KaziBantu* project aims at improving and promoting health literacy as a means for a healthy and active lifestyle. The project implements a school-based health intervention package consisting of physical education, moving-to-music, and specific health and nutrition education lessons from the *KaziKidz* toolkit. It is complemented by the *KaziHealth* workplace health intervention program for teachers.

**Objectives:**

The aim of the *KaziBantu* project is to assess the effect of a school-based health intervention package on risk factors for NCDs, health behaviors, and psychosocial health in primary school children in disadvantaged communities in Port Elizabeth, South Africa. In addition, we aim to test a workplace health intervention for teachers.

**Methods:**

A randomized controlled trial (RCT) will be conducted in 8 schools. Approximately 1000 grade 4 to grade 6 school children, aged 9 to 13 years, and approximately 60 teachers will be recruited during a baseline survey in early 2019. For school children, the study is designed as a 36-week, cluster RCT (*KaziKidz* intervention), whereas for teachers, a 24-week intervention phase (*KaziHealth* intervention) is planned. The intervention program consists of 3 main components; namely, (1) *KaziKidz* and *KaziHealth* teaching material, (2) workshops, and (3) teacher coaches. After randomization, 4 of the 8 schools will receive the education program, whereas the other schools will serve as the control group. Intervention schools will be further randomized to the different combinations of 2 additional intervention components: teacher workshops and teacher coaching.

**Results:**

This study builds on previous experience and will generate new evidence on health intervention responses to NCD risk factors in school settings as a decision tool for future controlled studies that will enable comparisons among marginalized communities between South African and other African settings.

**Conclusions:**

The *KaziKidz* teaching material is a holistic educational and instructional tool designed for primary school teachers in low-resource settings, which is in line with South Africa’s Curriculum and Assessment Policy Statement. The ready-to-use lessons and assessments within *KaziKidz* should facilitate the use and implementation of the teaching material. Furthermore, the *KaziHealth* interventions should empower teachers to take care of their health through knowledge gains regarding disease risk factors, physical activity, fitness, psychosocial health, and nutrition indicators. Teachers as role models will be able to promote better health behaviors and encourage a healthy and active lifestyle for children at school. We conjecture that improved health and well-being increase teachers’ productivity with trickle-down effects on the children they teach and train.

**Trial Registration:**

International Standard Randomized Controlled Trial Number (ISRCTN): 18485542; http://www.isrctn.com/ISRCTN18485542

**International Registered Report Identifier (IRRID):**

DERR1-10.2196/14097

## Introduction

### Background

Children’s health and well-being are influenced by cultural, environmental, and socioeconomic factors as well as living conditions and social and community networks [1]. In low- and middle-income countries (LMICs), infectious diseases remain an important public health problem [2-4] with negative impacts on child development [5]. Over 200 million children are infected with parasitic worms (helminths) [6,7] leading to chronic infections causing abdominal pain, diarrhea, and anemia, and may impair cognitive and physical development [8], which in turn might result in reduced fitness and work productivity [9]. In addition, helminth infections can negatively impact children’s nutritional status [10].

Although helminth infections and other neglected tropical diseases (NTDs) do not feature prominently in the burden of disease statistics of South Africa, some NTDs are common in disadvantaged populations, especially among children of poor communities [11]. The nutritional status of school children from poor neighborhoods is adversely affected by food outlets in close proximity to the schools. Indeed, many school children routinely purchase unhealthy foods from local vendors and tuck shops that are generally low in nutritional value, often refined, processed, and of low fiber content [12]. In a 12-country study (Australia, Brazil, Canada, Colombia, Finland, India, Kenya, People’s Republic of China, Portugal, South Africa, United Kingdom, and United States of America) [13], South African children showed the highest intake of sugar-sweetened beverages [14]. Schools located in poor communities in South Africa are part of the National School Nutrition Program, where members of the community, usually unemployed parents, are employed as food preparers. They do not have any food- or nutrition-related qualification.

A deprived socioeconomic environment can put children at risk of malnutrition resulting in growth retardation [15]. Studies have shown that malnutrition is associated with stunting and poor cognitive development, resulting in a low intelligence quotient, cognitive delays, and negative impact on motor development [15]. This, in turn, negatively affects children’s ability to concentrate, process information, and focus on academic tasks [16]. Children from low socioeconomic status (SES) families are also less likely to have access to health care or health insurance [17]. Together, this leads to a greater risk of illness, school absence, and ultimately poor academic performance and life prospects [18]. These deficiencies, caused mainly by the socioeconomic environment, can prevent school-age children from realizing their full potential and perpetuate a vicious cycle of poverty and poor health.

In addition, noncommunicable diseases (NCDs) are a rapidly evolving public health problem worldwide, especially in LMICs, imposing a growing burden on population health [2,19] including that of children [20]. Urban African populations have moved toward a disease profile similar to western countries, with increasing proportions of deaths attributed to chronic, lifestyle-related diseases [20]. The coexistence of under- and overnutrition has resulted in a double burden of nutrition-related diseases in Africa [21]. Children may, already at a young age, develop risk factors predisposing them to NCDs in adulthood [22,23]. Hence, children are at risk of compromised health because of a dual burden of disease, which may hamper their development and well-being [2,24]. Potential drivers of this double burden may be related to the shift in dietary habits and reduced energy consumption. This dual burden constitutes a large and growing challenge for health systems in African countries.

With up to 80% of all chronic diseases, stroke, and diabetes being preventable through healthy nutrition and regular exercise, more emphasis should be placed on prevention and awareness campaigns [25]. Physical education (PE) plays a critical role in holistic health education of the child. A randomized controlled trial (RCT) with Swiss elementary school learners (first and fifth graders) has shown that a 1-year school-based intervention can markedly improve physical activity and fitness, while simultaneously reducing obesity [26]. Regular physical activity contributes to the development of physical competence and fitness, as well as to the cognitive, social, and emotional development of the child [27]. As a rule of thumb, children should undertake at least 60 min of moderate-to-vigorous physical activity (MVPA) daily [28].

The Healthy Active Kids South Africa Report Card (2018) has shown that many children, particularly from marginalized communities, do not achieve the minimal daily requirements of MVPA [14]. Schools play an important role in making a meaningful contribution to the goal of achieving the recommended daily physical activity guidelines by incorporating PE lessons, among others, into the school curriculum. One plausible strategy to promote children’s health is through school-based health promotion programs. An attempt by a Swiss-South African research team to increase health literacy in South African children at school was the *Disease, Activity and Schoolchildren’s Health* (DASH) project [4]. The study focused on grade 4 children and the creation of an enabling school environment. The intervention program consisted of 4 main components, including (1) a medical examination and anthelmintic treatment, (2) micronutrient supplementation in the form of a nutrient-dense paste enriched with protein, essential vitamins (vitamin A), minerals, energy, and essential fatty acids, (3) health education (eg, hygiene and healthy nutrition), and (4) physical activity (dancing and playful games).

Our experiences with the DASH project also revealed that many South African teachers are at risk of cardiovascular diseases [29,30]. This insight was confirmed in a representative sample of South African educators (n=21,307) in public schools. Educators reported high stress levels, and there were significant associations between stress, lack of job satisfaction, and stress-related illnesses [31]. In South Africa, NCDs among adults have steadily increased. Indeed, although 42.90% (256,645/598,240) of deaths in 2005 were attributable to NCDs, the proportion rose to 57.40% (262,096/456,612) in 2016 [32]. Furthermore, in 2017, more than 1.8 million cases of diabetes were recorded in South Africa, representing 5.41% (1,826,100/33,762,000) of the adult population [33]. The project *Healthy Schools for Health Communities* presented here addresses this dual burden of disease, both in school children and teachers in South Africa (Figure 1).

**Figure 1 figure1:**
[figure not shown]
A conceptual framework of the *KaziBantu* study.

### Rationale

Having identified the potential for health status improvement among teachers and knowing the importance of teachers as role models in the education process of children, teachers will also participate in the proposed research project by involving themselves in a workplace health intervention. We will capitalize on the experiences from the aforementioned DASH project by scaling up the intervention program and monitoring and improving the efficacy and effectiveness of the intervention program. The goal of the *KaziBantu* project is to assess the impact of a school-based health intervention package on communicable diseases, risk factors for NCDs, health behaviors (beliefs and actions relating to health and well-being), and psychosocial health in primary school children in disadvantaged communities in Port Elizabeth, South Africa. In addition, we aim to test a workplace health intervention targeted at teachers.

## Methods

### Ethical Approval and Considerations

Ethical approval for the study has been received from the following ethics committees in Port Elizabeth, South Africa: (1) The Nelson Mandela University Ethics Committee (reference #H18-HEA-HMS-001; obtained on 26 March 2018), (2) Eastern Cape Department of Education (obtained on 9 May 2018), and (3) Eastern Cape Department of Health (reference #EC_201804_007; obtained on 5 June 2018). The study is registered at the ethical review board of the Ethics Committee Northwest and Central Switzerland (EKNZ; reference #R-2018-00047; registered on 1 March 2018).

On the basis of a uniform study information sheet, the investigators will explain to each participant (children and teachers) the purpose of the study, procedures involved, expected duration, and potential risks and benefits. Participation is voluntary, and hence, participants can withdraw at any time without any further obligations. All participants will be provided with an information sheet and a consent form describing the study. Individual medical information obtained during this study will be treated confidentially. Subject confidentiality will be ensured by utilizing subject identification code numbers to correspond to treatment data in password-protected computer files. For data verification purposes, authorized representatives of the EKNZ and the Nelson Mandela University Human Ethics Committee may require direct access to parts of the clinical records relevant to the study, including participants’ medical history.

### Study Area

The study will be conducted in historically black and colored primary schools in Port Elizabeth townships (Motherwell, Zwide, Kwazakhele, and New Brighton) and northern areas (Schauderville, Bethelsdorp, Windvogel, and Booysens Park), which form part of the Nelson Mandela Bay Municipality (Figure 2). These schools and communities are characterized by poverty and high unemployment rates. They represent the typical institutional and teacher-related PE barriers faced by the schools [34], including (1) shortage of qualified, accountable, and engaged PE teachers; (2) PE is marginalized as priority–it lost its standalone subject status in 1997 and is placed within the life skills and life orientation learning area, as more importance is given to other (examinable) subjects; (3) teachers lack the ability to integrate PE with other study areas within the life skills and life orientation subject (personal and social well-being, creative arts, and PE); (4) large class sizes; (5) insufficient and inadequate infrastructure and equipment; and (6) safety and security challenges.

**Figure 2 figure2:**
[figure not shown]
Study area (Port Elizabeth, South Africa) and location of the 8 schools participating in the *KaziBantu* study. Source: Kartendaten, AfriGID (Pty) Ltd.

### Study Design

The intervention arm targeting school children is designed as a 36-week RCT, including an intervention group (4 schools) and a control group (4 schools). The 4 intervention schools, assigned through randomization, will be further allocated randomly to the following intervention conditions: all schools will receive the teaching materials (*KaziKidz* and *KaziHealth*), but the components workshop and coaching will be assigned as follows: (1) teaching materials only, (2) teaching materials plus workshops, (3) teaching materials plus coaching, and (4) teaching materials plus workshops plus coaching (Figure 3).

The 4 remaining schools will be assigned to the control group. In the control schools, there will be documentation of routine PE and sports in school.

The primary comparison will be made between the 4 intervention schools and the 4 control schools to assess the benefit of teaching materials. Secondary comparisons will be between teaching materials plus coaching and teaching materials without coaching or teaching materials plus workshop and teaching materials without workshop. In view of the factorial design of our study, each comparison group consists of 2 schools.

By focusing on change in quantitative outcomes from baseline to follow-up, preexisting differences between schools should play less of a role. Although the intervention covers grades 1 to 7, in each school, 1 class each from grades 4, 5, and 6 will be randomly selected for evaluation of the intervention. After completion of the baseline assessment, children of the intervention schools will take part in a school-based health promotion program (32 school weeks, 1 PE lesson of 40 min per week, 1 moving-to-music lesson of 40 min per week, 3 health education lessons, and 3 nutrition education lessons of 40 min per year across the whole study period). The follow-up will be after 36 weeks (Figure 4). Qualitative data on the feasibility and acceptability of the intervention measures will also be collected from teachers through focus group discussions (FGDs).

For teachers, the study is designed as a 20-week RCT (Figure 5). The baseline assessment will also be offered to the teachers in the control schools. Intervention schools will be randomly assigned to the 4 different combinations of the additional components. After completion of the baseline assessment, all teachers will be informed about their personal health profile, providing an overview of cardiovascular health markers and mental health parameters. For each parameter, established internationally accepted cut-off and normative values will be used to estimate teachers’ health risks.

**Figure 3 figure3:**
[figure not shown]
A pictorial display of the *KaziBantu* study design.

**Figure 4 figure4:**
[figure not shown]
*KaziBantu* study design of testing the *KaziKidz* teaching material.

**Figure 5 figure5:**
[figure not shown]
*KaziBantu* study design of testing the *KaziHealth* tools.

The intervention program consists of the 3 main components discussed below.

#### Component 1: KaziKidz and KaziHealth Teaching Material

It is a holistic education and instructional tool designed for primary school teachers. This teaching material was pilot tested at 2 elementary schools in the Port Elizabeth area in August 2018. Feedback from teachers was obtained and the material revised accordingly. Through the implementation of 3 content pillars—(1) PE, (2) moving-to-music, and (3) health and hygiene and nutrition education lessons—the toolkit aims to enhance children’s overall health in disadvantaged South African primary schools. The *KaziKidz* teaching material consists of lesson plans within each of the 3 content pillars. The lessons have been designed in line with South Africa’s Curriculum and Assessment Policy Statement. Ready-to-use assessments can be found at the end of each section, which may be integrated into formal assessments of children’s performance and can complement the school's academic curriculum. The purpose is to lead children through content, games, and activities, partly supported by music and conducted in a joyful manner that encourages and promotes a healthy lifestyle throughout childhood and into adolescence. *Kazi* (an animated active mascot, designed to encourage children to participate in *KaziKidz*) and lesson plans will guide teachers through the teaching material. We expect that by using the *KaziKidz* teaching material, teachers will contribute to further the health and well-being of the children they teach and educate.

Physical activity: Regular physical activity opportunities (1 PE lesson of 40 min per week) will be incorporated into the main school curriculum in grades 1 to 7 over 32 weeks of the school year. A physical activity–friendly school environment will be created. These interventions are designed toward improving children’s physical activity levels and positively affecting their psychosocial well-being.The moving-to-music classes have been designed to promote physical activity through song and dance. The music utilized was developed by professional musicians from the Nelson Mandela University and is locally known and age-appropriate. Weekly lessons of 40 min each are designed with easy-to-follow illustrations that allow teachers to instruct without participating physically in the lessons. Schools or teachers who have a sound system available can make use of movement songs that have been created with cues specifically tailored to the lessons. Options for creating music through drums or any other form of percussion or clapping hands are also provided. Within the lessons, direct speech is used to address the children for easy application [35].Health, hygiene, and nutrition education: A series of classroom-based lessons have been developed [36]. School children will be educated on the prevention and treatment of intestinal parasite infections, such as proper hygiene, sanitation habits, and the importance of consuming clean water and food. By addressing these factors and educating children about appropriate health and hygiene behaviors, both the teachers and the school children are at a reduced risk of infection. Another series of classroom-based lessons will help to increase awareness about the importance of healthy nutrition. The South African National School Nutrition Program attempts to address micronutrient deficiencies and alleviate short-term hunger by providing food that supplies at least one third of the daily energy requirements of a child. To complement this, the nutrition education lessons (3x 40-min lessons per grade for grades 1-7) should bring dietetics closer to the learners in a playful way and encourage sustainable healthy eating habits throughout the learners’ lives. In addition, an analysis of the schools’ feeding program will be done to identify ways to improve their present diet. The food preparers in schools will also be trained in basic nutrition and hygiene during preparation of the school meals as unhygienic circumstances and poorly prepared meals can lead to infections and low nutrient intake [37].

*KaziHealth* is a workplace health promotion program that aims to educate and improve health behaviors among teachers. The program starts with an individualized health risk assessment followed by face-to-face lifestyle coaching sessions and self-monitoring and motivation through the *KaziHealth* mobile app. All teachers willing to participate in the program will undergo a comprehensive health risk assessment. In addition, teachers of the intervention schools will have the option to participate in a 20-week workplace health promotion program (Figure 6).

**Figure 6 figure6:**
[figure not shown]
The 20-week workplace health promotion program for teachers.

#### Component 2: Workshops

Teachers of 2 schools will participate in workshops for both *KaziKidz* and *KaziHealth.* The teaching content (lessons and assessments) of *KaziKidz* will be explained to the teachers before the implementation of the teaching material (2 sessions of 90 min each, as well as practical demonstrations and instruction at schools) and for *KaziHealth*, individually tailored lifestyle coaching workshops (2 sessions of 90 min each). The workshops will be relatively small (maximum of 20 teachers per workshop) and led by health professionals specializing in physical activity promotion, diet, nutrition, and psychosocial health. Furthermore, education, motivation, and self-monitoring will be provided through the *KaziHealth* mobile app [35] to assist individuals in making healthier lifestyle choices and decrease health risks. The *KaziHealth* mobile app [35] integrates 3 lifestyle interventions; namely, physical activity, nutrition, and stress management to guide individuals in achieving personal health goals. To test the efficacy of the workplace health promotion program over time, teachers will be assessed a second time after 20 weeks.

#### Component 3: Teacher Coaches

In the 2 schools where teachers will be offered coaching, trained sports students from the Department of Human Movement Science at the Nelson Mandela University will act as teacher coaches assisting the teachers in teaching and ensuring that the intervention is implemented in the schools correctly and as intensively as planned. Furthermore, they will also monitor the intervention process.

### Sample Size and Randomization

Assuming that the prevalence of obesity varies across schools according to a log-normal distribution with a mean value of 3% and a SD of 2%, 125 children per school in each of the 8 schools would provide a prevalence estimate between 1.5% and 5% with a probability of 95%. Under this assumption, 95% of school-specific prevalence would range between 0.8% and 8.2%. Hence, our aim is to recruit 125 children per school.

The power calculation for the intervention study is based on the change in a quantitative outcome variable from baseline to follow-up. We denote the SD of its change across schools and children by sigma (σ). Assuming an intervention effect size of 0.5 x σ and an intraclass correlation of .04 for the clustering of individual changes within schools (corresponding to a random effect SD of 0.2 x σ), 400 children in the 4 intervention schools (ie, 100 children per school) participating in baseline and follow-up, and 400 children in the 4 control schools would provide over 85% power to observe a statistically significant difference in the mean change of the respective outcome variable between intervention and control schools at the 5% level.

Enrollment of schools will be done by the local research team. To prevent contamination of the intervention effects, schools rather than classes were randomized in January 2019. Before randomization, schools were divided into 2 geographic groups; namely, township areas and northern areas, each containing 4 schools. Township areas are predominantly inhabited by black Africans and northern areas by colored people (after an apartheid-era classification, which refers to people from a multiracial ethnic background and can include persons of Khoi and San origin).

The randomization into intervention and control schools was done separately in each of the 2 groups so that each group was assigned 2 intervention and 2 control schools. To keep the design as balanced as possible, the 4 intervention schemes (ie, teaching materials only, teaching materials plus teacher workshops, teaching materials plus teacher coaching, and teaching materials plus teacher workshops plus teacher coaching) will be assigned in such a way that the intervention schools of 1 group will get teaching materials plus either teacher workshops or teacher coaching. Randomization will allow to determine which of the 2 groups gets which of the 2 pairs of intervention schemes. Sequentially numbered, opaque, sealed envelopes will be used for the assignment of the intervention arms to the schools.

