#### Data Collection and Statistical Analysis

The following data will be collected: (1) quantitative data on blood pressure, glycated hemoglobin and blood lipids, anthropometry and levels of physical fitness, cognitive performance and psychosocial health, (2) SES and demographic data, and (3) qualitative data on the feasibility and acceptability of the intervention measures implemented through FGDs. Quantitative data will be entered twice and cross-checked using EpiData version 3.1 (EpiData Association; Odense, Denmark). Cleaned data will be transferred to STATA version 13.0 (STATA Corp, College Station, TX, United States of America). Questionnaire data will be collected using the software package EvaSys (Survey Automation Suite, version 7.1) and analyzed with STATA.

Clinical and anthropometric indicators, physical fitness, cognitive performance, and psychosocial health values will be summarized by their mean and SD at normal distribution and otherwise by their median and interquartile ranges. Questionnaire information on psychosocial health will be expressed as a percentage.

For the analysis of cross-sectional and longitudinal associations, mixed linear or mixed logistic regression models will be used, depending on the type of outcome variable. These models will be adjusted for clustering within classes and schools using random intercepts. In analyses of cross-sectional associations, the models will include personal characteristics of children, such as gender and age, SES of parents or guardians, and other potential confounders of the associations of interest. Models assessing intervention effects will additionally include 3 indicator variables, as defined at the level of schools, 1 for schools of the intervention arm, 1 for schools receiving teacher workshops, and 1 for schools receiving teacher coaching. In addition, these models may include the value of the respective outcome variable at baseline. As intervention effects may also depend on the child’s initial characteristics, stratified analyses and analyses with interaction terms will be performed. Potential effect modifiers to be tested include gender, age, SES, ethnicity, health status, and physical fitness at baseline.

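### The stated power of over 85% at the 5% level holds only with a normal reference; with 8 randomised schools a valid two-sided test has about 75%

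*Protocol article*

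**What the plan says.** Under Sample Size and Randomization, the protocol article bases power on the change in a generic quantitative outcome, with σ as the SD of that change across schools and children. The inputs are:

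- Effect: "Assuming an intervention effect size of 0.5 x σ".
- Clustering: intraclass correlation 0.04 for changes within schools, equated to a school random-effect SD of 0.2σ.
- Size: "400 children in the 4 intervention schools (ie, 100 children per school) participating in baseline and follow-up"; the control arm is equally large.

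It concludes that this "would provide over 85% power to observe a statistically significant difference in the mean change of the respective outcome variable". The arms are to be compared at a significance level of 5%. It names no formula, sidedness, reference distribution or degrees of freedom.

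The same section says that schools were the randomised unit, in two geographic groups of four. Study Design makes the comparison of the 4 intervention with the 4 control schools primary. On the mixed models, Data Collection and Statistical Analysis says: "These models will be adjusted for clustering within classes and schools using random intercepts".

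**The concern.** When schools are randomised, the precision of the arm comparison depends mainly on the variance between schools, and here only 8 schools inform that variance. A calculation that treats it as known uses 1.96 as the critical value. A test that estimates it from 8 school means needs 2.447. The inputs do allow for clustering; the doubt is whether the result also allows for the small number of clusters.

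Two things are at stake. If the analysis is valid at 5%, the primary comparison has less power than claimed, and a null result would be over-interpreted. If the analysis relies on the normal reference, its nominal 5% test would produce false positives at about two to three times the claimed rate.

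**Working it through.** **Inputs** (Sample Size and Randomization; σ set to 1): effect 0.5; ICC 0.04, so between-school variance 0.04 and within-school variance 0.96; 100 children per school; 4 schools per arm; α = 0.05. Sidedness is not stated; two-sided is assumed and one-sided is shown below.

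**Step 1: standard error.**
- Variance of a school's mean change: 0.04 + 0.96/100 = 0.0496.
- SE of the 4 vs 4 difference: √(2 × 0.0496/4) = √0.0248 = 0.1575.
- Effect/SE: 0.5/0.1575 = 3.175.

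**Step 2: reproduce the stated figure.**
- Normal reference: Φ(3.175 − 1.960) = Φ(1.215) = 88.8%.
- Same result by design effect: 1 + 99 × 0.04 = 4.96; effective size 400/4.96 = 80.6 per arm; power 88.8%.
- Taking σ as the residual SD instead (variance 0.04 + 1/100) gives 88.5%.

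All of these agree with the article's claim.

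**Step 3: allow for 8 schools.** Degrees of freedom are 8 schools − 2 arms = 6. Noncentral t with noncentrality 3.175:

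| Setting | Critical value | Power |
|---|---|---|
| Normal, two-sided | 1.960 | 88.8% |
| t, 6 df, two-sided | 2.447 | 75.4% |
| t, 5 df (area fitted, explaining no variance) | 2.571 | 71.9% |
| t, 6 df, 125 children per school (variance 0.04 + 0.96/125 = 0.0477) | 2.447 | 77.0% |
| t, 6 df, unlimited children (variance 0.04) | 2.447 | 83.6% |
| t, 6 df, one-sided 5% | 1.943 | 87.4% |

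**Step 4: what would give 85% (t, two-sided).**
- Effect 0.57σ: noncentrality 0.57/0.1575 = 3.62, power 85.2%.
- Or an ICC of about 0.029: variance 0.029 + 0.971/100 = 0.0387, power 84.7%.
- Or 5 schools per arm (8 df): power 87.3%.

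**Step 5: type I error with a normal reference.**
- Analytically, P(|t₆| > 1.96) = 9.8%.
- In 400,000 simulated null trials of the balanced random-intercept model: REML with z 9.6%, ML with z 13.7%, t on 6 df 5.0%.
- Under the 0.5σ effect, simulated power is 87.1% for REML with z and 75.4% for t. The z test exceeds 85% only because it does not hold 5%.

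**Step 6: sensitivity to a class level.** The analysis model has a class intercept; the power inputs have no separate class term. Suppose an additional class ICC of 0.02 to 0.05 (assumed; the article gives none), with three classes per school as in Study Participants. The school-mean variance becomes 0.04 + 0.02/3 + 0.94/100 = 0.0561, up to 0.04 + 0.05/3 + 0.91/100 = 0.0658. Power on 6 df falls to 70% and 64%.

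**The case against.** The best defence is that the stated inputs do yield the stated figure, so nothing was miscalculated and the dispute concerns a reference distribution that the article does not name. That is accurate as a description of the cause. It does not save the claim, because over 85% power and a 5% level cannot both hold for a two-sided test on these 8 schools, whatever an unseen analysis plan says.

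Other points, in order of weight:

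- **Sidedness.** A one-sided 5% t-test on 6 df gives 87.4%. The article seeks a "statistically significant difference in the mean change of the respective outcome variable" and declares no one-sided test, so two-sided is the natural reading, but it remains an assumption.
- **Type I error.** The article specifies neither z tests nor ML, and an analysis plan may contain a small-sample correction. The error rates are therefore conditional, and omission of that detail from an article is not itself a fault. The power shortfall does not depend on it.
- **Class level.** If the 0.04 already absorbs class clustering, power stays near 75%. The 70% to 64% range is illustrative only.
- **Covariates.** Area could explain between-school variance. If it explained 10% (assumed), the variance would be 0.04 × 0.9 + 0.0096 = 0.0456 and power on 5 df would return to 75.4%. If baseline adjustment removed 20% of the variance (assumed), 6 df power would be 83.9%. The power statement claims no such gain, and neither case reaches 85%.
- **Model terms.** The intervention models also carry workshop and coaching indicators. The arm coefficient is then the materials-only effect, with SE √(0.0496 × (1/4 + 3/4)) = 0.223; power for 0.5σ is 61% by z and 40% by t on 4 df. The 75% therefore belongs to the simple 4 vs 4 contrast only.
- **Timing.** Randomisation and the baseline survey are complete, so correction cannot change the design. It still changes how results are tested and read.

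**Conclusion.** The concern holds. On the article's own inputs, power for the primary 4 vs 4 comparison is 75.4%, at least 10 points below the stated figure. The chance of missing a true 0.5σ effect is about 25%, where the article implies under 15%. At an ICC of 0.04, no number of children in 8 schools reaches 85%. This rests on a two-sided 5% test and on estimating the between-school variance from 8 schools.

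The doubling of type I error (about 10% with REML, about 14% with ML) applies only if tests use the normal reference. The class-level and area figures are sensitivity illustrations and the conclusion does not need them.

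**What to change.** Restate power as about 75% for a 0.5σ effect with a two-sided t reference on 6 df (about 72% if area is fitted and explains no variance), or state 0.57σ as the effect detectable with 85% power. Tie the figure explicitly to the simple comparison of 4 intervention with 4 control schools, since it does not apply to the arm coefficient in the three-indicator model.

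For the analysis, state that the linear mixed models are fitted by REML with Kenward-Roger or Satterthwaite degrees of freedom, or use a t-test on adjusted school-level mean changes, in place of z tests. If the analysis plan already does this, only the power statement needs correction.

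The cost is a less favourable stated figure and wider confidence intervals. No schools or children need be added.
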